### Participant and setting

2.1

Patients will be consecutively recruited from the Department of Orthopedics, Skåne University Hospital, Sweden (main site) and the Department of Orthopedics, Oslo University Hospital, Oslo, Norway. The majority of patients (approx. 70%) will be included in Sweden. The study is approved by The Regional Ethical Review Board in Lund, Sweden (Dnr 2016/319) and Oslo, Norway (REK sør-øst D: 2016/1128).

*Inclusion criteria*: i) one year (between 10 and 16 month) after ACLR, with or without associated injuries to other structures of the knee (e.g., collateral ligament(s), meniscal injury), ii) age 18–35 years. *Exclusion criteria*: i) previous serious injury or surgery to either knee (e.g., ACL tear, meniscal tear), ii) diseases or disorders overriding the knee condition (e.g., neurological disease), iii) contra-indicators for MRI, iv) not understanding the languages of interest (any Scandinavian language or English). Possible confounders to record at the assessments include: i) additional surgery to the index knee between the time point of ACLR and inclusion and/or during follow-up, ii) serious injury to the index knee (e.g., giving-way episode(s)) resulting in pain and/or swelling and requiring inpatient or outpatient health care between the time point of ACLR and inclusion and/or during follow-up. Demographics (e.g., age sex, BMI, heredity) and other patient-reported outcomes will be collected at baseline and at follow-up (See Table 1 for full details). As a sample of convenience, 20 age- and sex-matched non-knee injured individuals will be recruited among students in Lund, Sweden. With the exception that these individuals should be free from ACL injuries to both knees, the inclusion/exclusion criteria will be the same for this cohort as for the patient cohort.

**Table 1 tbl1:** Demographics and patient-reported outcomes to be collected at baseline and at follow-up.

	Baseline		Follow-up	
	ACLR patients	Controls	ACLR patients	Controls

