### Assessments

2.2

All predictors and outcomes will be assessed at 1 year (baseline) and at 3 years (follow-up) after ACLR. *Primary predictor* is knee extension muscle strength at baseline. *Secondary predictors* are knee flexion, hip, and trunk muscle strength, hop performance, postural orientation and patient-reported outcomes (except patient-reported pain) at baseline. *Exploratory predictor* is muscle activation pattern at baseline. *Main outcome* is the Knee injury and Osteoarthritis Outcomes Score (KOOS), subscale pain at follow-up. *Secondary outcome* is T2 (MRI) and biomarker profiles at follow-up (full description of predictors and outcomes are outlined below and in Table 1, Table 2). One physical therapist researcher will perform all functional assessments in Lund and another physical therapist researcher will perform all functional assessments in Oslo. The researchers will give standardized verbal instructions and an inter-rater reliability testing has been performed, showing moderate to excellent inter-rater reliability for all functional assessments (ICC_2*K*_ 0.66–1.0) (See Appendix A for detailed description of the reliability assessment).

**Table 2 tbl2:** Predictors and outcomes at baseline and follow up.

Predictors at baseline and follow-up for ACLR patients	Data collection instrument

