#### Patient-reported outcomes

2.3.5

Data for the following valid questionnaires will be collected and managed using an electronic data capture tool (REDCap) [33] (Lund) or using paper questionnaires (Oslo); The Short-Form 36 [34] will be used for assessment of perceived generic health. For patient-reported knee specific function, the KOOS (all subscales except pain) [35], Global knee function: Numeric Rating Scale (1–10 were 1 = worst and 10 = best) [36]and the ACL Quality of Life [37] will be used. The Tegner activity scale [38] will be used to assess pre-injury and current activity level and the ACL Return to Sport after Injury Scale [39] will be used to evaluate psychological readiness for returning to sport after injury. In addition, the participants will answer a questionnaire regarding their pre-injury activity, if they plan to return/have returned to the same activity or different activity level as well as time point of return (if any). Finally, the Perceived stress scale - 10 [40] will be used for perceived stress.

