#### MR image acquisition

2.4.3

Subjects will be positioned in a supine position with their feet first in a 1.5 T MRI scanner (AvantoFit, Siemens Healthcare, Erlangen, Germany) and the injured knee placed in a knee coil (TxRx 15 Ch Knee, Siemens, Erlangen, Germany). After localizer sequences, four 2D proton density weighted turbo spin echo sequences will be acquired for scoring and clinical evaluation with: 1) sagittal orientation and no fat suppression, and 2–4) sagittal, transversal and coronal orientations with fat suppression. For T2 mapping, two sagittal slices positioned in the central part of each of the medial and lateral tibiofemoral cartilage compartments, respectively, will be acquired in a single, interleaved acquisition using a 2D multi echo spin echo sequence with 12 echoes. Finally, a sagittal T1 weighted 3D VIBE (Volumetric Interpolated Breath Hold Examination) sequence will be acquired for segmentation of the bone. Imaging parameters for each sequence are summarized in Table 3.

**Table 3 tbl3:** Image acquisition parameters for the proton-density weighted turbo-spin echo (PDW TSE), multi-echo spin echo (MESE) and T1 Weighted Volumetric Interpolated Breath Hold Examination (3D T1W VIBE) sequences.

Sequence	PDW TSE	PDW TSE	PDW TSE	PDW TSE	MESE	T1W VIBE
Orientation	Sagittal	Sagittal	Coronal	Transversal	Sagittal	Sagittal
2D/3D	2D	2D	2D	2D	2D	3D
Fat suppression	None	Fat Sat	Fat Sat	Fat Sat	None	Water excitation
Echo time (ms)	41	45	37	38	10–120	6
Repetition time (ms)^a^	3000	4550	3000	3760	2360	14
Flip angle						10
Turbo factor	10	11	5	5	12	
Field of view (mm^2^)	160×160	170×170	150×150	160×160	145×160	150×150
Voxel size (mm^3^)	0.4×0.4×3	0.5×0.5×3	0.5×0.5×3	0.5×0.5×3	0.4×0.4×3	0.3×0.3×0.6

a May vary slightly as the number of slices will be adjusted for coverage in each case.

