### Statistical analysis

2.5

For descriptive purposes, the mean (SD), or median (quartiles), at baseline and follow-up assessments will be used as appropriate. Separate linear regression models will be used to elucidate the influence of the absolute values of each predictor on the absolute value on primary, secondary and exploratory outcomes in cross-sectional analyses and on the absolute value as well as change in primary, secondary and exploratory outcomes in longitudinal analysis, adjusted for baseline values and possible confounders (e.g., age and associated injuries). In addition, logistic regression analysis will be used to elucidate the influence of each predictor on significant knee pain (KOOS pain ≤72 vs > 72). Assuming a clinically relevant correlation of 0.30 between knee extension strength and self-reported pain [50], we need 84 patients with 80% power at the 5% significance level. Based on this calculation, we will include 100 patients including an approximate drop-out of 15%. For explorative purposes, an analysis of covariance (ANCOVA) will be used to investigate differences in the presence of early knee OA between the 100 patients with ACLR and twenty sex and age matched non-injured individuals, adjusting for activity level.

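### The exploratory patient-versus-control ANCOVA pools two sites against controls from one, so about 30% of any Lund-Oslo difference would enter the contrast; a site term or a Lund-only comparison removes this at little cost.

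*Protocol article*

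**What the plan says.** Participant and setting names two patient sites, "Skåne University Hospital, Sweden (main site) and the Department of Orthopedics, Oslo University Hospital, Oslo, Norway", and gives the split: "The majority of patients (approx. 70%) will be included in Sweden". About 30% of patients therefore come from Oslo. The controls are a convenience sample from one place: "20 age- and sex-matched non-knee injured individuals will be recruited among students in Lund, Sweden". No Oslo controls are planned.

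Statistical analysis fixes the comparison of the two groups. It opens with "For explorative purposes, an analysis of covariance (ANCOVA) will be used" and sets the contrast "between the 100 patients with ACLR and twenty sex and age matched non-injured individuals, adjusting for activity level". Matching is on sex and age, and activity level is the only covariate named. Site is not named as a matching factor, a covariate or a restriction.

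Comparing the prevalence of early knee osteoarthritis (OA) in patients and non-injured controls is stated as an additional aim at the end of the Introduction.

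**The concern.** Every control is a Lund participant, but only about 70 of the 100 patients are. In a pooled model without site, anything that shifts Oslo values relative to Lund values, other than the injury, moves the patient mean and leaves the control mean where it is. Possible sources are image acquisition, blood collection and storage, and background differences between the two populations. The model would attribute that shift to ACLR.

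The article shows that the sites do not work identically. Questionnaires are collected with an "electronic data capture tool (REDCap) [33] (Lund) or using paper questionnaires (Oslo"), and while one researcher tests in Lund, "another physical therapist researcher will perform all functional assessments in Oslo". These two facts do not themselves establish a difference in T2 or serum markers. At stake is the interpretation of the control comparison only.

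**Working it through.** **The plan's own figure.** The article gives no sample size or power for the ANCOVA. Its one calculation is for the primary correlation: r = 0.30, 80% power, 5% level (taken as two-sided), 84 patients. Fisher's z gives ((1.960 + 0.842) / atanh 0.30)² + 3 = 84.9, so 85. A t-based variant gives 79.96% power at 84. Dropout: 84 / 0.85 = 98.8, so 99, against 100 stated. The figure reproduces and is not affected by this point.

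**Inputs.** From Participant and setting: about 70 Lund patients, about 30 Oslo patients, 20 Lund controls. From Statistical analysis: 100 versus 20, activity level as covariate. Assumed: an Oslo-minus-Lund difference d in SD units of the outcome, which the article does not give.

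**Bias.** Bias = (Oslo share among patients − Oslo share among controls) × d = (0.30 − 0) × d.

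**Standard error with outcome SD = 1.** Pooled: √(1/100 + 1/20) = 0.245.

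**Rejection rate when injury has no effect.** An unmodelled site difference also inflates the residual variance. The site indicator has a within-patient sum of squares of 100 × 0.30 × 0.70 = 21, so the residual variance is about 1 + 21d²/118. The estimated SE is then 0.245 × √(1 + 21d²/118), while the estimate itself varies with SD 0.245.

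| d (SD, assumed) | Bias (SD) | Residual variance | Estimated SE | Rejection rate, formula | Rejection rate, simulated ANCOVA |
|---|---|---|---|---|---|
| 0.25 | 0.075 | 1.011 | 0.246 | about 6% | not run |
| 0.5 | 0.15 | 1.045 | 0.250 | 8.7% | 8.6% |
| 1.0 | 0.30 | 1.178 | 0.266 | 18.4% | 18.3% |

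Worked line for d = 1: the upper tail is P(Z > (1.96 × 0.266 − 0.30) / 0.245) = P(Z > 0.90) = 0.183, and the lower tail adds less than 0.001.

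The simulation used 4,000 runs, normal errors and an activity covariate balanced between groups. With d = 0 the pooled model rejected in 4.8% of runs.

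**Sensitivity to the Oslo share.** With d = 0.5, a share of 20% to 40% gives a bias of 0.10 to 0.20 SD.

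**With site in the model.** In the same simulation the bias was about 0 and the rejection rate was 5.0% to 5.7%.

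**Cost in precision.**

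- Baseline, 70 versus 20: √(1/70 + 1/20) = 0.254, and 0.2535 / 0.2449 = 1.035. The difference detectable with 80% power is 2.80 × SE: 0.69 SD pooled, 0.71 SD within Lund.
- Follow-up, assuming 15% patient dropout at each site and all 20 controls retained: √(1/85 + 1/20) = 0.2485 and √(1/59.5 + 1/20) = 0.2585, a ratio of 1.04.

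The cost is small because the 20 controls contribute most of the variance: 0.05 of the pooled 0.06.

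**The case against.** **The analysis is exploratory and the offset is unknown.** Both are true. The sample size does not rest on this contrast, and nothing in the article documents a Lund-Oslo difference in T2 or serum markers. The 1 SD case marks the end of an assumed range and is not an expectation.

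**The article contains safeguards.** MR image acquisition describes one machine type, a "1.5 T MRI scanner (AvantoFit, Siemens Healthcare, Erlangen, Germany"), with one coil. T2 maps come from one application, one reader draws all regions of interest, and the biomarkers are assayed in batch. These limit measurement differences. They do not cover blood collection and storage or background population, and the article does not say where the Oslo patients are scanned.

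**The documented site differences may not reach this contrast.** Table 1 marks the KOOS questionnaire for patients only, although the outcome heading in Table 2 covers patients and controls. If controls do not complete it, electronic versus paper collection is irrelevant here. The functional assessors measure predictors, not these outcomes. The point therefore rests on T2 and, if controls give blood, on the biomarkers.

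**A condensed article need not list every covariate.** That is fair in general. For the regressions, the article does leave the confounders open by giving examples. For the ANCOVA, it names the pooled 100 patients and a single adjustment, so this is a stated model.

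**Stronger readings that the article does not support.**

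- A reader might infer that site could explain the whole control comparison. Site and injury are only partly confounded, because about 70 patients share the controls' site. At an offset of 0.5 SD the bias is 0.15 SD, less than one standard error.
- A reader might count differences in associated injuries between sites as bias. The eligibility criteria admit those injuries on purpose, so they belong to the ACLR population being compared.
- A reader who holds the residual SD at 1 would get 9.4% and 23.2% for offsets of 0.5 and 1 SD. That shortcut ignores the inflated residual variance and overstates the error of the stated analysis.

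**Conclusion.** The point holds as a cheap improvement to an exploratory analysis. As stated, the ANCOVA lets about 30% of any non-injury Lund-Oslo difference into the injured-versus-control contrast. For assumed offsets of 0.5 and 1 SD, the bias is 0.15 and 0.30 SD and the rejection rate is about 8.6% and 18% instead of 5%. At 0.25 SD or less the harm is small.

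These figures assume a 70/30 patient split, an additive site difference, similar activity levels in the two groups and a two-sided 5% test. Whether an offset exists, and how large it is, cannot be determined from the article. The primary within-patient regression and its sample size are unaffected.

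**What to change.** In Statistical analysis, make the main control comparison either the ANCOVA with site added or a comparison of Lund patients with Lund controls (about 70 versus 20). Report the pooled two-site comparison without site as a sensitivity analysis.

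The two options are close but not identical. With a site term, the Oslo patients still contribute to the activity slope and the residual variance. With restriction they do not.

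The change takes about one sentence and no new data. It widens the standard error by about 3.5% at baseline (detectable difference about 0.71 instead of 0.69 SD) and about 4% at follow-up. The contrast then rests on the Lund patients, and the report should say so. It would also help to state where the Oslo patients are scanned.

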## Discussion

3

To our knowledge, our study will be the first to investigate the role of different measures of muscle function as possible protective factors for possible markers of early OA development including patient-reported pain, MRI, and biomarkers in patients with ACLR. There is today no consensus regarding the definition of early symptomatic OA in younger individuals with a history of knee injury [10]. Several different models, such as a cut-off of 72 on the KOOS pain subscale, the minimally clinical reported difference (KOOS pain) and a combination of different cut-offs of the different KOOS subscales have been proposed [10]. In this study, we chose the cut-off of 72 on the KOOS pain subscale since this measure is reported to be related to cartilage loss [11] as well as knee pain in patients with ACL injury [9]. Furthermore, we will include both advanced measures of muscle function (isometric muscle strength assessed with a Biodex) and those that are easily administered in clinical research and in the clinical setting (performance-based measures). If muscle function will be a protective factor for possible markers of early OA, this will have important clinical implications for using muscle function as screening for knee OA at an early stage of the disease, and for optimizing muscle function in the treatment of knee injury. Further studies may determine whether exercise aimed at improving important aspects of muscle function may prevent, or slow the progression of, early signs of knee OA. By addressing muscle function as a modifiable factor to prevent, or slow the progression of, knee OA, this project ultimately has the potential to influence clinical management at an early stage of this chronic disease, and reduce the personal and societal burden of this increasing health problem.

